### Team participants

Fifteen teams of ten Māori or Pacific Island smokers, total of 150, participated in this study. There were five teams from each region.

### Team coaches

In addition there were 15 coaches. The team coaches were not part of the team, but where selected, in addition to the team, in a support role.

### Inclusion criteria for research

Self-identified smokers aged 18 years and over and willing to take part in the research were eligible to participate. Smoking status was validated using exhaled carbon monoxide (CO) and to be eligible to enter, participants needed to have a baseline CO rating greater than 6 ppm.

### Exclusion criteria for research

People, who would not provide written consent for their participation, non-smokers or very light/infrequent smokers whose exhaled carbon monoxide (CO) was less than 7 ppm at entry, were excluded from the study. To ensure the competition was being tested with smokers, biochemical verification at entry was thought desirable, thus very light or infrequent smokers would likely be excluded.

### Power calculations

Assuming 80% power, 5% significance, 1-sided test, no design effect, and a standard treatment 3 month quit rate of 24% (from the National Quitline), the study would need approximately 100 persons total to detect a target 3 month quit-rate of 35%. However, because the drop-out rate at follow-up is assumed to be high (50% from past studies), 150 smokers were recruited.

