#### WERO intervention

WERO participants compete in teams of ten current smokers, the majority of which knew each other prior to the intervention, which boosts peer social support and enable the dynamics of whanaungatanga (a relationship through familial and shared experiences) to operate. Each team appoints a ‘coach’ whose role is to encourage their team and facilitate team meetings and activities. Criteria for the coaches are that they are non-smokers or ex-smokers, and that they are willing to support their team to quit over the contest period.

The team with the most smokefree members at the end of the competition wins. If multiple teams have the same number of smokefree team members, one winner will be randomly drawn by a computer random digit generator. The prize of $5000 goes to their nominated charity or community organisation. If a team member tries to cheat the competition, team members would continue to receive support to quit but they would be excluded from the prize draw.

WERO participants are encouraged and supported to use NRT, such as, nicotine patches, gum or lozenges, which in New Zealand can be obtained using a Quitcard for as little $5 for 8 weeks supply. They are also told about Champix (varenicline) and Zyban (bupropion) which are subsidised, but only available on prescription. The *New Zealand smoking cessation guidelines* recommend NRT be used for a course of at least 8 weeks [51], thus the WERO competition period will run for 3 months.

An interactive website and iPad app is used to strengthen the sense of team and inter-team competitiveness by making the smoking status of team members and the team as a whole publicly visible. To keep all teams up-to-date on their own and other team’s performances, weekly updates of smoking status are requested from the regional Coordinators. Teams and supporters are also able to post questions, comments or support, to the team page. Frequent interaction with the website should help reduce relapse, and will be encouraged with the use of a prize of $500 for the team that utilises their team page the most. In addition, the website and app provides information in the style of tips on quitting and relapse prevention. Participants’ questions or comments about withdrawal symptoms and trigger situations on their web page can also be answered and commented on by the study’s primary investigator, an expert in smoking cessation.

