### Regional coordinators

WERO co-ordinators, an identified person at regional level who can facilitate local use of WERO, will be appointed for each region. A District Health Board (DHB) healthy lifestyles team have been subcontracted to promote WERO and recruit teams in Northland. An urban Auckland Māori authority Whānau Ora provider have been subcontracted to deliver WERO to their urban population, and a Pacific Island WERO Co-ordinator was employed to work with Pacific Island churches. In addition to implementing the intervention, the WERO co-ordinators will also act as a research assistant and collect data.

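### The sample size assumes no design effect although smokers take part in 15 intact teams of ten, so the stated requirement of about 100 is too small for any positive within-team correlation

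*Protocol article*

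**What the plan says.** The Power calculations section of the protocol article gives its terms as "Assuming 80% power, 5% significance, 1-sided test, no design effect". The reference rate is "a standard treatment 3 month quit rate of 24% (from the National Quitline"), and the result is that "the study would need approximately 100 persons total to detect a target 3 month quit-rate of 35" per cent. The only allowance above that number is for attrition: "the drop-out rate at follow-up is assumed to be high (50% from past studies), 150 smokers were recruited".

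Elsewhere the article describes a grouped design:

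- Team participants: "Fifteen teams of ten" make up the 150, and "There were five teams from each region".
- WERO intervention: "WERO participants compete in teams of ten current smokers, the majority of which knew each other prior to the intervention". Each team has its own coach and web page, and the main prize goes to the charity or organisation named by the team with the largest number of quitters.
- Regional coordinators: at least one provider was "subcontracted to promote WERO and recruit teams in Northland", so the unit approached there was the team.

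The Measures section makes the main analysis intention-to-treat and counts anyone lost to follow-up as a smoker. It names no test for the primary outcome, and the article mentions no confidence interval.

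**The concern.** The intervention is meant to work through the group: people with existing ties, encouraged by the same coach, sharing a public page and pursuing a common prize. Members of one team can therefore be expected to have more similar outcomes than members of different teams. Setting the design effect to 1 assumes that away, and the article offers no reason for doing so. This is an assumption the article states, not a detail left to an analysis plan.

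The study has no concurrent control, so the comparison with 24% is its only quantified benchmark for effectiveness. The Discussion foresees a rapid roll-out if the programme works. If 150 clustered people are treated as 150 independent ones, the planned precision is overstated. If the analysis made the same assumption, the evidence against 24% would look stronger than it is.

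**Working it through.** **Inputs from the article.** p0 = 0.24, p1 = 0.35, one-sided alpha 0.05 (z = 1.645), power 80% (z = 0.842), 15 teams, team size m = 10, 150 recruited. All 150 stay in the denominator because missing counts as smoking.

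**Assumed.** ICC of 0.02, 0.05, 0.10 or 0.20, since the article gives none. The 35% is taken as the rate after missing people have been counted as smokers.

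**1. Reproduce the stated figure.** One-sample test against a fixed 24%:

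n = [1.645 × √(0.24 × 0.76) + 0.842 × √(0.35 × 0.65)]² / 0.11²
= (0.702 + 0.401)² / 0.0121 = 100.7, so 101.

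This agrees with about 100. A two-sided version gives 127 and a two-arm comparison gives 212 per arm, so the one-sample, one-sided reading with independent individuals is the one that fits.

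**2. Add clustering.**

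- Design effect DE = 1 + (10 − 1) × ICC
- Required N = 100.7 × DE
- Effective N = 150 / DE
- Power = Φ{[0.11 × √(effective N) − 1.645 × √(0.24 × 0.76)] / √(0.35 × 0.65)}

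| ICC | DE | Required N before dropout | Effective N of 150 | Power, 150 analysed |
|---|---|---|---|---|
| 0 | 1.00 | 101 | 150 | 91% |
| 0.02 | 1.18 | 119 | 127 | 87% |
| 0.05 | 1.45 | 147 | 103 | 81% |
| 0.10 | 1.90 | 192 | 79 | 72% |
| 0.20 | 2.80 | 282 | 54 | 59% |

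Power equals 80% when 100.7 × DE = 150, that is, at ICC = (150/100.7 − 1)/9 = 0.054.

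**3. What would follow if the analysis also ignored teams.** The size of an unadjusted one-sided z-test is 1 − Φ(1.645/√DE). The exact binomial rule for n = 150 rejects at 46 or more quitters; its size was computed from the sum of 15 independent beta-binomial teams of ten. Coverage of an unadjusted 95% interval is 2Φ(1.96/√DE) − 1.

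| ICC | Size, z-test | Size, exact rule | Coverage of a 95% interval |
|---|---|---|---|
| 0 | 5.0% | 3.7% | 95.0% |
| 0.02 | 6.5% | 5.1% | 92.9% |
| 0.05 | 8.6% | 7.0% | 89.6% |
| 0.10 | 11.6% | 9.8% | 84.5% |
| 0.20 | 16.3% | 14.1% | 75.9% |

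**The case against.** A reader might infer that the trial's 5% error rate and its confidence intervals are wrong. The article does not support that. It names no primary test and gives no interval, and the design-effect statement appears only as an input to the sample size. A full protocol or analysis plan, not shown, may well account for teams. The second table is therefore conditional. Its size also depends on the ICC: at 0.01 the exact rule still has a size of 4.4%, and the figures of 14–16% need an ICC of 0.20, which nothing in the article establishes.

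A reader might also infer that true power is below the stated 80%. That is not shown either. The 150 recruited exceed the 100 required, and with all 150 analysed power stays at or above 80% up to an ICC of about 0.054. A simulated t-test on the 15 team proportions gives lower power (80%, 73%, 62% and 46% at the four ICCs). Part of that drop reflects the test itself, whose simulated size is only 2.9–3.9%, so it should not all be put down to clustering.

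Finally, the assumption is openly disclosed, recruitment is reported as complete, the article uses the word pilot, and its abstract says more rigorous testing is warranted. These points limit the consequences. They do not justify an ICC of zero in a team-based design, and the stated requirement of about 100 rests on exactly that value.

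**Conclusion.** The sample-size basis contradicts the design the article describes. The figure of about 100 holds only with an ICC of zero; over the assumed range of 0.02 to 0.20 the requirement before dropout is 119 to 282. At an ICC of 0.05 it is 147, so clustering alone uses almost all of the increase from 100 to 150 that the article attributes to dropout.

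The effect on power is moderate at low ICCs and serious at high ones, from 87% down to 59%. These figures rest on equal teams of ten, on all 150 being analysed, and on 35% already counting missing people as smokers. If 35% was meant as the rate among those followed up, power would be lower. Inflated type I error and intervals that are too narrow follow only if the analysis also ignores teams, which the article leaves open.

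**What to change.** In Power calculations, replace the no-design-effect assumption with power restated for 15 teams of ten over a stated ICC range, for example 0.02 to 0.10, with the reason for choosing that range.

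State that the primary quit rate will be compared with 24% by a method that accounts for team, with a matching confidence interval. A one-sample t-test on the 15 team proportions (14 df) is one option; a cluster-robust method with a small-sample correction is another. They are alternatives with different small-sample behaviour, not equivalents, so one should be named in advance. Report the observed ICC, which any follow-on trial will need.

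The cost is small. Team membership is already needed to score the competition, and no further enrolment is proposed. The price is a wider interval and a less favourable stated power, and the t-test gives up some further power through its conservatism.

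### The 50% dropout allowance does not turn 100 into 150, and it treats dropout as lost sample size although the main analysis counts losses as smokers

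*Protocol article*

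**What the plan says.** The Power calculations section of the protocol article sets the terms: "Assuming 80% power, 5% significance, 1-sided test, no design effect", with a reference 3-month quit rate of 24% taken from the National Quitline and a target of 35%. On these terms "the study would need approximately 100 persons total". The next sentence gives the reason for the larger number enrolled: "However, because the drop-out rate at follow-up is assumed to be high (50% from past studies), 150 smokers were recruited". The Team participants section confirms the total: "Fifteen teams of ten Māori or Pacific Island smokers, total of 150, participated in this study".

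The Measures section, which follows directly, defines the outcome being powered. This is biochemically validated smoking status at the end of the 3-month competition. The main analyses are by intention-to-treat, and anyone lost to follow-up is taken to be smoking.

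**The concern.** There are two separate faults.

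- **The arithmetic.** The step from 100 to 150 multiplies by 1.5. An allowance for 50% loss has to divide by 0.5.
- **The model of dropout.** Adding recruits to cover dropout makes sense only if people who drop out leave the analysis. Under the Measures section they stay in the denominator as treatment failures. Dropout then leaves n alone and reduces the proportion counted as quit.

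At stake is how the result will be read. The only stated power is 80%, and the number enrolled is presented as protecting it against heavy loss. A reader facing a null result cannot tell whether the study was well powered, underpowered or almost certain to fail. The answer depends on what the 24% and 35% refer to, and the protocol does not say.

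**Working it through.** **Inputs.** From Power calculations: p0 = 0.24, p1 = 0.35, one-sided 5% (z = 1.645), 80% power (z = 0.842), "no design effect", requirement about 100, dropout 50%, recruited 150. From Measures: intention-to-treat, losses counted as smoking. From the opening of Methods/Design: a pre-test post-test design without a concurrent control.

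**1. Reproducing the requirement.** One-sample test of a proportion against a fixed rate, normal approximation:

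n = [(1.645 × √(0.24 × 0.76) + 0.842 × √(0.35 × 0.65)) / 0.11]² = 100.7

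This agrees with about 100. A two-group one-sided comparison would need 212 per group, so the one-sample reading is the one that fits. Power at n = 100 is 79.8%. The 100 is therefore a requirement before any dropout.

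**2. The allowance.**

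- Needed for 100 followed up: 100/(1 − 0.5) = 200.
- What was done: 100 × (1 + 0.5) = 150.
- Followed up out of 150 at 50% loss: 150 × 0.5 = 75, which is 25% below 100.
- Loss that 150 does cover: 1 − 100/150 = 33%.

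**3. Power on each reading.** Normal approximation: power = Φ[(0.11 − 1.645 × √(p0(1 − p0)/n)) / √(p1(1 − p1)/n)]. The exact figures use the binomial distribution with the smallest critical count whose one-sided error is at most 5%.

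| Reading | n | True rate in the analysis | Power, normal | Power, exact |
|---|---|---|---|---|
| A. Completers only | 75 | 35% | 70.0% | 66.0% (25 or more quit) |
| B. Intention-to-treat, 35% among all enrolled | 150 | 35% | 91.2% | 88.5% (46 or more quit) |
| C. Intention-to-treat, 35% among those followed up | 150 | 0.35 × 0.5 = 17.5% | practically nil | below 0.01% (46 or more quit) |

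**4. What reading B demands.** A 35% rate among 150 is 52.5 quitters. With half lost they must all come from the 75 followed up: 52.5/75 = 70%. Even bare significance, 46 of 150, needs 46/75 = 61% of those followed up to have quit.

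**5. Sensitivity of reading C to the loss.** The intention-to-treat rate is 0.35 × (1 − loss). It falls to the 24% reference when loss = 1 − 0.24/0.35 = 31%. At the one-third loss that 150 would cover, it is 0.35 × 2/3 = 23.3%, already below the reference. Recruiting 200 would not help on this reading, because the rate at 50% loss stays 17.5% whatever the n.

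**The case against.** The strongest reply is that the Measures section removes the problem. With losses counted as smokers, all 150 are analysed. If 35% is meant as the rate among everyone enrolled, power is about 91%, above the stated 80%. The protocol also attaches 80% to the 100, and never says in terms that 150 would leave 100 or that 80% survives 50% loss. Recruitment is reported as done, so nothing in the design can change.

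Much of this stands. In particular, a reader might infer from the wrong allowance that the trial has 75 evaluable participants and that its real power is 70%. The documents do not support that for the main analysis. Someone lost to follow-up is evaluable there, as a smoker, and the denominator is 150. The 70% belongs to a completers-only test that the protocol does not plan as its main analysis.

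The reply does not rescue the stated justification. If 35% already counts losses as smokers, dropout gave no reason to enrol more than 100, and the target implies that 70% of those followed up quit. If 35% does not count them, the main analysis has practically no power at the assumed loss. Either way the sentence linking 50% dropout to 150 is wrong as written.

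**Conclusion.** The point holds in two parts. First, the allowance fails on its own inputs: 200, not 150, would be needed for 100 followed up at 50% loss. Second, Power calculations treats dropout as lost sample size while Measures treats it as failure to quit, and the two are not reconciled. As a result, no single power figure can be given for the main analysis: it is about 91% (88.5% exact) or practically nil, according to a definition that the protocol leaves open. It would be equally unsupported to conclude that the study is simply underpowered or that it is comfortably powered.

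These figures assume a one-sample test against a fixed 24%, which the protocol does not name but which reproduces its 100. They take the 50% loss to apply at 3 months, the time point being powered, because the text says only that it is at follow-up. They keep the protocol's assumption of no design effect; positive correlation within the teams of ten would lower the figures for readings A and B. The 24% reference carries the same ambiguity as the 35%, and the comparison is like for like only if both treat losses in the same way.

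**What to change.** Keep the 150 and change the wording of Power calculations:

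1. Correct the arithmetic: at 50% loss, 200 recruits would be needed for 100 followed up; 150 leaves 75 and covers a loss of one third.
2. State whether the 24% and the 35% each count people lost to follow-up as smokers.
3. Restate power for the intention-to-treat analysis at n = 150 on that definition, with the assumed loss and the quit rate it implies among those followed up.
4. If the completers-only figure is given at all, label it as such: about 70% (66% exact) at n = 75.

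No change to recruitment, data collection or analysis is needed. The cost is that the stated justification for 150 goes, and the power reported may be less favourable than 80%.

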### Measures

The main outcome will be biochemically validated smoking status at the end of the competition. Main analyses will be carried out on an intention-to-treat basis. Participants lost to follow-up will be assumed to be smoking. Since quit and win can have high rates of deception, smoking status will be assessed using CO tests pre and post contest. CO tests were chosen for pragmatic reasons, namely its low cost, ease of use and its availability for healthcare providers. It is limited however to detection of active smoking within the previous 2-5 hours only [52], but unfortunately other methods are cost-prohibitive [53]. The CO tests were used to determine which team will win the prize. Secondary outcomes will be self-reported point prevalence at 6 months follow-up, use of pharmacotherapy, duration until relapse, tobacco consumption, and activity on the website. Because there will not be any incentives for participants’ to be smokefree at 6-months follow-up, the risk of deception is lower than at end of competition. Therefore, self-reports was considered sufficient. Furthermore, not doing a CO test at 6 months was also about reducing research burden for participants and research assistants, and using self-report enabled follow-up to be conducted by telephone.

At baseline and 3 months follow up exhaled CO will be measured using a Bedfont Smokerlyzer CO monitor. The amount of CO in ‘end-expired air’ is a good approximation for the concentration of CO in the blood and exhaled CO levels will be higher in smokers than in non-smokers. There is however no agreement about what the optimal cut-off point is. Middleton and Morice [54] found a cutoff level of 6 ppm, which detected 94% of smokers and 96% of non-smokers in a respiratory outpatient clinic. In this study a relatively low cutoff point of 6 ppm will be used, because there is low air pollution in New Zealand [55].

At baseline, 3 and 6 months participants will be asked to complete paper-based questionnaires with 33 close-ended questions (Table 1). These questionnaires are used to determine the progress of the participants and to determine the short-term effects of the competition.

**Table 1 T1:** Questionnaire topics

**Category**	**Topic realms**
Demographic	Sex, ethnicity, age, marital status, education level, community service card (proxy for socioeconomic status)
Smoking behavior	Smoking status, amount smoked, time to first cigarette, previous cessation attempts and methods used.
Quitting behavior	Number of quit attempts, any support used to quit, reason for quitting and interest in cessation support
Others smoking	Presence of smokers in participants’ social networks? Does anyone else in the house smoke? Do people smoke indoors?
WERO – related	Reasons for stopping during WERO? Cessation methods of interest? Relationship with other team members? Competition methods that help team smoking cessation? Social support by family and friends.
Technology	Access to mobile phone, IPad/tablet, Internet? Use of social networking sites.

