Interventions that have shown promise internationally are stop smoking competitions where usually individuals who smoke stop for a chance to win a prize of cash or products. Quit and win competitions have run all over the world since the early 1980s [6] with long term quit rates ranging from 8% to 20% at 12-months [7]. Short term quit rates at the end of the competition have been as high as 66% [8]. Only a few quit and win competitions have focused on disadvantaged population groups. However, one quit and win competition aimed at low-income smokers in the United States had significantly higher overall quit rates in the treatment group with 23% (compared to 9% in the control group) still quit at 12-months [9]. Māori and Pacific Island people in NZ are overrepresented among lower socio-economic groups [10,11]. A quit and win competition was piloted in 2000 in the Hawke’s Bay region of New Zealand and achieved quit rates of 40% at 12 months follow-up [12]. The competition included a high proportion of Māori (32% compared to 22% of the total Hawkes Bay population).

Given NZ’s heightened urgency to increase quitting on a mass scale, and the positive potential for quit and win competitions to be attractive to and more effective at bringing about cessation among smokers from lower socio-economic groups it is time to test quit and win competitions for Māori and Pacific Island people [13]. We propose a quit and win competition which is aligned more with Indigenous people’ cultural principles and beliefs. The main aim of this paper is to describe how knowledge of Indigenous people’s practices and principles can be incorporated with proven effective smoking cessation support into a culturally appropriate cessation intervention WERO (WERO in the Māori language means challenge). Included in the aim is describing identified cultural principles and practices that can be used in a cessation competition and describing identified effective cessation elements that could be incorporated. A final aim of the paper is to describe the WERO study protocol.

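### The sample is enlarged to replace dropouts, but the primary analysis keeps dropouts in the denominator as smokers, so the power statement does not match the planned analysis

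*Protocol article*

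**What the plan says.** Protocol article, Power calculations: the design values are "Assuming 80% power", "5% significance, 1-sided test, no design effect", and "a standard treatment 3 month quit rate of 24% (from the National Quitline"). The result is "approximately 100 persons total to detect a target 3 month quit-rate of 35"%. The next sentence raises the number: "However, because the drop-out rate at follow-up is assumed to be high (50% from past studies), 150 smokers were recruited".

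Protocol article, Measures: the main outcome is biochemically validated smoking status at the end of the 3-month competition. The main analyses are intention-to-treat, and "Participants lost to follow-up will be assumed to be smoking".

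Protocol article, Background, on earlier contests: "Short term quit rates at the end of the competition have been as high as 66"%. The denominator of that figure is not given.

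The article does not say whether 24% and 35% are rates among everyone enrolled or among those followed up.

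**The concern.** Recruiting extra people to cover dropout makes sense when dropouts leave the analysis and the aim is to keep enough observed outcomes. Under the rule in Measures nobody leaves: all 150 are in the denominator, and each person lost counts as a smoker. Dropout then lowers the quit rate itself, and a larger sample only estimates the lowered rate more precisely.

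The design has no concurrent control arm, so the conclusion rests on one observed proportion set against 24%. If the 35% was meant for those followed up, the study could fall short of the reference through attrition alone, even if the programme did what the planners hoped. If the 35% was meant for everyone enrolled, the article justifies the step from 100 to 150 with the wrong argument and leaves unstated how well the retained participants must do.

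**Working it through.** **Inputs.** From Power calculations: reference rate p0 = 0.24, target p1 = 0.35, one-sided 5%, 80% power, dropout d = 0.50, N = 150. From Measures: ITT denominator, lost to follow-up = smoking.

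**1. Reproduce the plan's figure.** One proportion against a fixed reference, normal approximation:

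n = [(1.645·√(0.24·0.76) + 0.842·√(0.35·0.65)) / (0.35 − 0.24)]² = [(0.702 + 0.401) / 0.11]² = 100.7.

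This agrees with the stated figure of about 100. The enlargement to 150 equals 100 × 1.5. (Dividing by 1 − d would give 200, but that is a separate matter and nothing below depends on it.)

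**2. Effect of the missing-data rule.**

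ITT quit rate = (1 − d) × quit rate among those retained.

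With 150 enrolled and 50% lost, 75 are retained, but the denominator stays at 150.

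**3. Rejection rule at N = 150.** The exact one-sided binomial test against 24% rejects at 46 or more quitters (30.7%; actual size 3.7%).

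**4. Reading A: 35% is the rate among those followed up.** The ITT rate is 0.35 × 0.50 = 17.5%, and P(X ≥ 46 | 150, 0.175) = 0.00006, or about 0.006% power. At other dropout levels:

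| Dropout | Expected ITT rate | Exact power, N = 150 |
|---|---|---|
| 0% | 35.0% | 89% |
| 10% | 31.5% | 62% |
| 20% | 28.0% | 26% |
| 30% | 24.5% | 5% |
| 50% | 17.5% | 0.006% |

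The expected ITT rate falls below the reference once dropout exceeds 1 − 0.24/0.35 = 31%.

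**5. Reading B: 35% is the ITT rate.** P(X ≥ 46 | 150, 0.35) = 88.5%, above the planned 80%, and no dropout allowance is called for. The rate needed among those retained is 0.35/(1 − d): 44% at 20% dropout, 50% at 30%, 58% at 40% and 70% at 50%. At 50% dropout, reaching the 46 quitters needed for significance takes 46/75 = 61% of those retained.

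**6. What N = 150 can detect on the ITT scale.** Exact power is 75.5% at an ITT rate of 33.0% and reaches 80% at about 33.6% (33.0% by the normal approximation). The implied rates among those retained are:

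- 50% dropout: 0.336/0.50 = 67%
- 30% dropout: 0.336/0.70 = 48%
- 20% dropout: 0.336/0.80 = 42%

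All of these ignore clustering by team, as the article's own calculation does.

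**The case against.** The strongest reply is that Measures makes ITT with missing = smoking the main analysis, so 35% should be read as an ITT rate. Power is then 88.5%, and the only faults are an unneeded enlargement and an unstated rate among those retained. That reading is open and the text does not exclude it. But the stated reason for 150 is then wrong, and the dropout allowance itself points to thinking in terms of those followed up.

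A reader might infer that the 35% target is incompatible with 50% dropout. The documents do not support that: with half lost, the ITT rate can still reach 50%, so 35% is hard but attainable. A reader might also infer that 70% of those retained exceeds anything seen in earlier contests, because Background cites a maximum of 66%. That figure has no stated denominator. If it counts all entrants, the right comparison is with 35%, which it far exceeds. Background also cites a New Zealand pilot with 40% quit at 12 months, again with no denominator. The 66% is a loose benchmark only.

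The 50% is given for follow-up without naming the visit, and there are follow-ups at 3 and 6 months. It stands inside a calculation for the 3-month rate, so 3 months is the likelier meaning, though not a certain one. The Discussion hopes that team support will keep attrition low, but the planning figure is still 50%.

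The 24% Quitline rate may already count non-responders as smokers. The article does not say. If it does, the comparison is like for like, but the 70% requirement stands.

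Finally, counting the lost as smokers is not itself an error, and a sensitivity analysis for missing outcomes is something an article may leave to the full protocol or analysis plan. Neither is part of this point.

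**Conclusion.** The point holds as an inconsistency between the sample-size rationale and the primary analysis, and it should be fixed. The defect lies in Power calculations, not in the missing-data rule. Its size depends on a denominator that the article leaves open: power of about 0.006% if the rates refer to those followed up, or 88.5% with a 70% quit requirement among those retained if they refer to everyone enrolled. Neither reading supports enlarging the sample to replace dropouts. It would go too far to say that the study has no chance of success, because that follows on only one of the two readings.

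The figures assume a one-sample exact binomial test against a fixed 24%, 150 in the denominator, 50% dropout at 3 months and no clustering.

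**What to change.** In Power calculations:

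- State that 24% and 35% are ITT quit rates with missing counted as smoking, and confirm that the Quitline 24% is on the same basis.
- Delete the dropout-replacement rationale for 150.
- Restate power for that estimand: N = 150 gives 80% exact power for an ITT rate of about 33.6% (33.0% by normal approximation), ignoring clustering.
- Report the implied quit rates among those retained: about 67%, 48% and 42% at 50%, 30% and 20% dropout.

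Keep missing = smoking as the primary rule. The cost is rewording one section; no additional participants or data are needed. The only drawback is that the stated assumption about those retained will look less favourable.
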